**Figure 3 figure3:**
[figure not shown]
Community advisory board–informed topics, content, and structure for the intervention. Forum topics track the adapted sIMB conceptual framework. PrEP: pre-exposure prophylaxis; sIMB: situated Information, Motivation, and Behavioral skills; STI: sexually transmitted infection.

Beta testing of the app and intervention was carried out with the CAB to get a sense for how the features will work in the subsequent pilot trial. The CABs were oriented to the app and were asked to use it for a month. During the beta testing, 4 semistructured discussions were convened that mimicked how anticipated sessions will occur during the actual trial. The CAB members reconvened with the study team to provide feedback on their experiences, which was used to make the necessary final changes to the intervention prior to the randomized controlled trial.

#### Piloting and Evaluating the PrEP US NoW Intervention

The primary outcomes from the trial will include feasibility and acceptability, improvement in social capital, and reduction in internalized homonegativity. Secondary outcomes will include estimates of intervention efficacy in increasing PrEP uptake and decreasing condomless anal sex acts. Figure 4 outlines the study design for the pilot intervention.

**Figure 4 figure4:**
[figure not shown]
PrEP US NoW study design. One-to-one randomization will be done prior to this, with control arm indexes (n=10) to refer 8-10 young, Black, sexual minority men from their social network. These network referrals will be screened for eligibility, undergo sociograms, and then have access to the HealthMpowerment app alone, with surveys at T0, T1 (at 1 month), and T3 (at 3 months). mHealth: mobile health; PrEP: pre-exposure prophylaxis; PrEP US NoW: Pre-Exposure Prophylaxis Utilization Through Increasing Social Capital Among Young, Black, Sexual Minority Men Networks With Women.

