To recruit networks of young, Black, sexual minority men, index young, Black, sexual minority men participants will be recruited first, who will subsequently recruit up to 8 young, Black, sexual minority men members of their own social networks. Similar resources and strategies used earlier will be used to recruit index young, Black, sexual minority men participants. Inclusion criteria for young, Black, sexual minority men index participants are (1) age 18-29 years, (2) HIV negative (based on self-performed HIV OraQuick test), (3) Black cisgender men (based on gender and sex at birth), (4) self-reported past sex with other men (past 6 months), (5) English speaking, and (6) able to identify 6-8 young, Black, sexual minority men in their personal social network. The exclusion criterion is cognitive impairment resulting in the inability to provide consent. Potential index participants will complete a web-based screening survey to determine eligibility. Once an individual is considered eligible, they will be contacted (via phone or in person) to provide more details about the study and will be asked to complete an informed consent. Enrolled index young, Black, sexual minority men participants (n=12) will be randomized (2:1) to the intervention arm (n=30, 6 indices with 5 network members per index) or the control arm (n=30, 6 indices with 5 network members per index). The allocation sequence is generated and assigned by REDCap (Research Electronic Data Capture), and participants are enrolled by our research coordinator. The allocation is computer-generated for randomization by our REDCap. Allocation concealment is provided by the REDCap system. Participants' IDs are provided to our data manager, who enters this information into REDCap. They then inform our research coordinator of the randomization arm for the participant. Both the intervention and control arms will be unblinded. At recruitment, the participants will be educated on the protocol and goal of the study, understanding how support systems can improve access to HIV prevention strategies like PrEP. The randomized controlled trial was registered within ClinicalTrials.gov (NCT07024745).

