#### Intervention Arm

A total of 6 young, Black, sexual minority men's social networks, each including 5 young, Black, sexual minority men (including index participants) and 1 Black female facilitator, will participate in the intervention arm. Before the trainings, the Black female facilitators completed a baseline survey electronically, which measured sociodemographics, HIV knowledge, PrEP knowledge, HIV-related stigma [53], homophobia [54], and PrEP stigma. Black female facilitators have completed their training on app usage. In addition, Black females also completed an (web-based or face-to-face) intensive training covering (1 day) cultural competence and humility when working with sexual and gender minority populations; experiences of stigma among young, Black, sexual minority men in the South; LGBTQ-focused sexual health topics; and basic information about HIV treatment and prevention, including the use of PrEP and steps required to engage in PrEP care.

All young, Black, sexual minority men in the intervention arm will also receive a training (web-based or face-to-face), including a tour of the downloadable US NoW app, a brief demonstration of how to join and participate in the web-based discussion, and practice on posting content publicly and privately. Once trained, young, Black, sexual minority men will complete HIV testing using OraQuick rapid HIV test (remote participants will be asked to text a picture of the test result via a secure server) and an electronic baseline survey prior to study commencement capturing information on sociodemographics, stigma related to race or ethnicity and sexual practices or orientation [55,56], HIV, poverty, PrEP use [57], PrEP knowledge [57], sexual history and practices [58], alcohol [59] and substance abuse [60], and depression [61] and anxiety [62], using appropriate validated measures. In the event an individual tests positive on an HIV test, they will be referred to the linkage team at the study site’s university-affiliated clinic for counseling, access to confirmatory testing, and linkage to care, if necessary.

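### Index men are randomized before they refer their networks in an unblinded trial, so 48 of 60 participants can be selected and consented after their cluster's arm is known

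*Protocol article*

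**What the plan says.** **Order of steps.** The Figure 4 caption reads "One-to-one randomization will be done prior to this, with control arm indexes (n=10) to refer 8-10 young, Black, sexual minority men", and continues: "These network referrals will be screened for eligibility, undergo sociograms, and then have access to the HealthMpowerment app alone". The Recruitment, Screening, and Consent section is consistent with this order: "index young, Black, sexual minority men participants will be recruited first, who will subsequently recruit up to 8" members of their own networks, and "Enrolled index young, Black, sexual minority men participants (n=12) will be randomized (2:1) to the intervention arm".

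**Who knows the arm.** REDCap generates and conceals the sequence. The data manager enters the participant ID and passes the arm to the research coordinator, who is also the person who enrols participants. The section adds: "Both the intervention and control arms will be unblinded". At recruitment, "the participants will be educated on the protocol and goal of the study", in both arms.

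**Room for choice.** An index must be able to name 6-8 men and may recruit up to 8. The Sample Size Justification needs four per index: 12 indices and 60 men in all.

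**Baseline.** In the Intervention Arm section, men first receive a training on the US NoW app and its discussions. Then: "Once trained, young, Black, sexual minority men will complete HIV testing using OraQuick rapid HIV test", together with the electronic baseline survey. The Control Arm section gives controls the same tests and surveys and describes no training.

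**Analysis and limitations.** Data Analysis plans GEE logistic models with an exchangeable working correlation within index, adjusted for sociodemographic, stigma, knowledge, sexual-history, substance-use and mental-health covariates. The Discussion considers selection bias only as volunteers against the general population, not as one arm against the other.

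**The concern.** This is a cluster-randomized design in which most cluster members are found after the cluster has been allocated. Randomization then protects the comparison of the 12 indices, but not the make-up of the networks they assemble. An index who expects facilitated group discussions of stigma, sexual health and PrEP has reason to approach different friends from an index who can offer only an app. The coordinator who screens and enrols those friends knows the arm, and the friends themselves may accept or decline because of it.

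Such a shift would appear in the between-arm estimates of social capital and internalized homophobia (primary outcomes) and of PrEP uptake (secondary). Feasibility and acceptability are less exposed. The Results section makes promising findings the condition for seeking funding for a fully powered trial, so a recruitment artefact could influence that decision and the sequence could be carried into the larger design.

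In the intervention arm, the baseline measurement also follows allocation. Men who withdraw, or answer differently, because they know their arm do so before baseline is recorded, so the baseline data cannot fully reveal or correct the imbalance.

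**Working it through.** **1. Share of participants exposed.** Inputs from Sample Size Justification: 12 indices, 4 others each.
- Members recruited after allocation: 12 × 4 = 48. Total: 12 × 5 = 60. Share: 48/60 = 80%.
- Recruitment, Screening, and Consent speaks of 5 network members per index. If that meant five besides the index, the share would be 60/72 = 83%. The stated 30 per arm (6 × 5) and the Intervention Arm section, which counts the index among the five, support 48 of 60.

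**2. The plan's own margins.** The plan states ±12% and ±25% at 50%, and ±9% and ±18% at 15%, for correlations 0 and 0.9. Normal approximation: 1.96 × √(p(1−p) × DE/n), with DE = 1 + (5−1) × ICC, so DE = 1 at ICC 0 and 4.6 at ICC 0.9. The last column is a simulated cluster bootstrap with 12 clusters of 5.

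| p | ICC | Stated | Normal, n = 60 | Bootstrap, 12 clusters |
|---|---|---|---|---|
| 50% | 0 | ±12 | 12.7 | 11.6 |
| 50% | 0.9 | ±25 | 27.1 | 24.9 |
| 15% | 0 | ±9 | 9.0 | 8.3 |
| 15% | 0.9 | ±18 | 19.4 | 16.4 |

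All four stated margins are within 2 points of the bootstrap when all 60 men are pooled. They describe one proportion over the whole sample, not one arm and not a difference.

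**3. Margins that fit a between-arm question, at 15%.**
- One arm of 30, ICC 0: 1.96 × √(0.15 × 0.85/30) = 12.8 points (cluster bootstrap with 6 clusters: 10.7).
- Difference of two arms of 30, ICC 0: 1.96 × √(2 × 0.15 × 0.85/30) = 18.1 points.
- At ICC 0.9, multiply by √4.6 = 2.14: about 27 and 39 points by the normal approximation.

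**4. Illustrative bias with no intervention effect (assumed, not from the document).**
- Suppose three extra men in the intervention arm would have started PrEP anyway: 3/30 = 10 points. Expected adopters at 15% are 0.15 × 30 = 4.5, so this is two-thirds more. Spread over the 6 × 4 = 24 referred members of that arm, it is 3/24 = 12.5 points.
- More generally, let referred members of the intervention arm differ by d points in PrEP use at entry, with 15% in controls and 80% of men referred. The arm difference is 0.8 × d.

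| d | Arm difference | Odds ratio with no effect |
|---|---|---|
| 5 | 4 | 1.33 |
| 10 | 8 | 1.69 |
| 15 | 12 | 2.10 |
| 20 | 16 | 2.55 |

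For d = 10: (0.23/0.77)/(0.15/0.85) = 1.69.

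**5. What the analysis can remove.** GEE with robust standard errors allows for correlation within networks. It does not move a point estimate that is shifted by who was recruited. Covariates can absorb part of the shift, but there are only 12 clusters, the covariates are measured after allocation in the intervention arm, and the listed set does not name PrEP use at baseline, although the baseline survey records it.

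**The case against.** **The timing rests on a caption.** The figure is not shown, and the caption's allocation ratio, number of control indices and number of referrals disagree with the text (2:1 with 6 and 6 indices, up to 8 referrals, four needed). Those figures must be reconciled. The text does not expressly time randomization against referral. This stands as a caveat. However, the caption assigns the referral task to indices already labelled as control, the text has enrolled indices randomized and members recruited later, and nothing in the document gives another order or a safeguard.

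**Members' knowledge of the arm is not stated.** A reader might infer that every network member knows his arm when he consents. The document says only that the arms are unblinded, not when members are told. What it does establish is that the enrolling coordinator is informed. That the index knows is probable, and that members know at consent is only possible.

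**Contaminated baseline.** A reader might infer that the training itself changes baseline stigma or PrEP answers. As described, it is an app tour, a short demonstration and posting practice, before any discussion takes place. A direct effect is probably small. What remains is arm awareness and differential refusal before baseline.

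**A shift larger than the plan's error margin.** A reader might set the 10-point illustration against the ±9% in the Sample Size Justification and conclude that the bias exceeds the sampling error. That is not supported, because the ±9% matches all 60 men pooled. Against the margins for one arm or for the difference, 10 points lies inside.

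**Existing limits and pilot status.** Having to be able to name 6-8 men narrows an index's later choice, and covariate adjustment helps somewhat. Neither removes the problem. The pilot is sized for feasibility and precision, which lowers the severity but does not answer the point for the between-arm outcomes.

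**Conclusion.** The point holds as a structural weakness: 48 of 60 men (80%) can be selected, approached and consented after their cluster's allocation is known to the enroller and probably to the index, and no safeguard is described. This assumes that the caption's order is the one followed. The planned GEE with covariates can correct the resulting bias only in part.

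Neither the direction nor the size of the bias can be derived from the document. Three extra would-be adopters would add 10 points of uptake without any effect. That is large against an anticipated 15%, but inside about ±13 points for one arm and ±18 for the difference at zero correlation, and further inside at higher correlation. The bias therefore need not stand out from chance in this pilot, but it is systematic, and a larger trial with the same sequence would not average it out.

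It should be fixed where it still can be. It does not invalidate the pilot, and its feasibility and acceptability findings are largely unaffected.

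**What to change.** **Networks not yet allocated.** Reorder the existing steps. The index completes the sociogram and his referrals. All five men are screened, consented, HIV tested and surveyed at baseline. Only then is the index ID entered in REDCap and the arm released. App training follows. State this sequence in the text and in the Figure 4 caption.

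**Networks already allocated.** Report baseline PrEP use and stigma by arm and by index versus member, together with the numbers referred, screened and enrolled per index. State the possibility of recruitment bias as a limitation of the between-arm estimates of social capital, internalized homophobia and PrEP uptake.

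**Cost.** A protocol amendment and a change in order, using procedures already planned. Indices must wait while their network is assembled, for a time the document does not allow one to estimate. Some participants may be lost meanwhile, which matters because the Discussion expects that some men will be unstably housed. Baseline surveys began in August 2024, so the reordering may reach only some networks. The reporting step applies to all the others.

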#### Recruitment, Screening, and Consent

A network-based approach was used to identify social network members of the index young, Black, sexual minority men participants by following a sociogram protocol [52], that is, graphic plotting of the young, Black, sexual minority men’s social network members. The recruitment for young, Black, sexual minority men is still ongoing, whereas recruitment for Black female group facilitators has been completed. For each index young, Black, sexual minority man in the intervention arm, a Black female social network member, referred by the CAB and external to the young, Black, sexual minority men's network, was screened. The inclusion criteria for the Black women facilitators included (1) self-identified Black race and female gender, (2) age >18 years, and (3) fluency in written and spoken English. The goal was to have at least one eligible Black female member per 6 eligible young, Black, sexual minority men, serving as a facilitator in each group. The ultimate Black female facilitator selection only consisted of cisgender women and was made by the CAB based on a structured interview to assess stigmatizing beliefs and cultural humility. As this was an egocentric network analysis, the investigators assumed networks were independent of one another; however, the first name and last initial of participants were collected to evaluate for overlaps across networks in the analyses.

To recruit networks of young, Black, sexual minority men, index young, Black, sexual minority men participants will be recruited first, who will subsequently recruit up to 8 young, Black, sexual minority men members of their own social networks. Similar resources and strategies used earlier will be used to recruit index young, Black, sexual minority men participants. Inclusion criteria for young, Black, sexual minority men index participants are (1) age 18-29 years, (2) HIV negative (based on self-performed HIV OraQuick test), (3) Black cisgender men (based on gender and sex at birth), (4) self-reported past sex with other men (past 6 months), (5) English speaking, and (6) able to identify 6-8 young, Black, sexual minority men in their personal social network. The exclusion criterion is cognitive impairment resulting in the inability to provide consent. Potential index participants will complete a web-based screening survey to determine eligibility. Once an individual is considered eligible, they will be contacted (via phone or in person) to provide more details about the study and will be asked to complete an informed consent. Enrolled index young, Black, sexual minority men participants (n=12) will be randomized (2:1) to the intervention arm (n=30, 6 indices with 5 network members per index) or the control arm (n=30, 6 indices with 5 network members per index). The allocation sequence is generated and assigned by REDCap (Research Electronic Data Capture), and participants are enrolled by our research coordinator. The allocation is computer-generated for randomization by our REDCap. Allocation concealment is provided by the REDCap system. Participants' IDs are provided to our data manager, who enters this information into REDCap. They then inform our research coordinator of the randomization arm for the participant. Both the intervention and control arms will be unblinded. At recruitment, the participants will be educated on the protocol and goal of the study, understanding how support systems can improve access to HIV prevention strategies like PrEP. The randomized controlled trial was registered within ClinicalTrials.gov (NCT07024745).

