##### Sample Size Justification

For this pilot study, the importance of sample size lies in establishing feasibility and the precision of estimated changes, which will inform the design of future studies. Twelve index participants will be recruited, and each index will provide information to recruit 4 others, yielding a total sample size of 60. Six indexes will be randomized to PrEP US NoW and 6 to the control group. The clustering of participants within the index (specifically the PrEP US NoW group) may result in a reduced effective sample size. Assuming no correlation within indices for all participants, a rate of advancement of 50% for PrEP US NoW, the bootstrap 95% CI would have a margin of error of ±12%. On the other hand, assuming a large correlation, 0.9, the margin of error becomes ±25%. With an anticipated 15% PrEP uptake, the 95% CI margin of error is ±9% for no correlation and ±18% for a correlation of 0.9.

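### The allocation ratio is given as 2:1 beside two equal arms, as one-to-one with 10 control indexes, and as 6 and 6; the passages must be reconciled and checked against the ratio loaded in REDCap

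*Protocol article*

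**What the plan says.** Four places in the protocol article bear on the allocation.

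- **Recruitment, Screening, and Consent** (the operative sentence): enrolled index "participants (n=12) will be randomized (2:1) to the intervention arm (n=30, 6 indices with 5 network members per index"). The same sentence then gives the comparison arm identical numbers, six indexes and 30 men. The section adds that REDCap generates and assigns the sequence.
- **Figure 4 caption**: "One-to-one randomization will be done prior to this, with control arm indexes (n=10) to refer 8-10 young, Black, sexual minority men".
- **Sample Size Justification**: "Twelve index participants will be recruited, and each index will provide information to recruit 4 others, yielding a total sample size of 60". It continues: "Six indexes will be randomized to PrEP US NoW and 6 to the control group".
- **Intervention Arm**: six networks, "each including 5 young, Black, sexual minority men (including index participants) and 1 Black female facilitator". The Results section repeats the six groups of five men and expects 30 men in the control arm.

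**The concern.** The allocation ratio and the number of randomized units are basic design facts, and the article gives them in ways that cannot all be true. The recruitment sentence contradicts itself: a 2:1 ratio does not go with two arms of six indexes. The Figure 4 caption contradicts that sentence on the ratio, and contradicts both that sentence and the sample size section on the number of control indexes.

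REDCap produces the sequence, and the article names the ratio outright only twice, once as 2:1 and once as one-to-one. A reader cannot tell from the document which list is in use. If it is a 2:1 list, the planned arms of 30 and 30 would not be the expected result, and more networks would need a facilitator than the six planned. Baseline surveys of the men began in August 2024 and recruitment was still open when the article was written, so allocations may already have been made from the list.

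**Working it through.** **1. Reproduce the plan's sample size.** Inputs from Sample Size Justification: 12 indexes, each with 4 others.

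- Total: 12 × (1 + 4) = 60.
- Per arm at 6:6: 6 × 5 = 30.

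This agrees with the n=30 per arm in the recruitment sentence, with the six networks of five men under Intervention Arm, and with the 30 control men in Results.

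**2. Put each stated ratio through the same arithmetic** (5 men per network).

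| Statement | Indexes | Men | Matches a stated arm size? |
|---|---|---|---|
| 2:1 on 12 indexes | 12 × 2/3 = 8 and 12 × 1/3 = 4 | 40 and 20 | No |
| 1:1 on 12 indexes | 6 and 6 | 30 and 30 | Yes |
| One-to-one with 10 control indexes | 10 and 10 = 20 | 100 in all | No |
| 10 control indexes with 6 intervention networks | 6 and 10 = 16 | 80 in all | Intervention arm only |

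A 2:1 permuted-block list completed at 12 gives exactly 8:4. Under simple 2:1 randomization the chance of exactly 6:6 is 924 × (2/3)^6 × (1/3)^6 = 11.1%, where 924 is the number of ways to choose 6 of 12.

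**3. Do the stated margins depend on the ratio?** Formula: 1.96 × √[p(1−p)/n × (1 + 4 × ICC)], for networks of 5.

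| Rate, ICC | Stated | n = 60, normal approximation | n = 60, finite-cluster / simulated bootstrap | n = 30, normal approximation |
|---|---|---|---|---|
| 50%, 0 | ±12% | 12.65% | 12.55% / 12.4% | 17.9% |
| 50%, 0.9 | ±25% | 27.1% | 26.0% / 24.9% | 38.4% |
| 15%, 0 | ±9% | 9.0% | 9.0% / 8.6% | 12.8% |
| 15%, 0.9 | ±18% | 19.4% | 18.6% / 15.9% | 27.4% |

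As a set, the four stated figures fit all 60 men pooled and not one arm of 30. (A simulated bootstrap for six networks gives 17.2%, 31.4%, 12.0% and 17.7%; only the last is near its stated value.) The pooled margins, like the total of 60, are the same at 6:6 and 8:4.

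**4. What 8:4 would do to the arm comparison.** The article gives no margin for the difference between arms, so this is our own calculation. At a 50% rate and ICC 0:

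- 6:6: 1.96 × √[0.25 × (1/30 + 1/30)] = 25.3%.
- 8:4: 1.96 × √[0.25 × (1/40 + 1/20)] = 26.8%.

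At ICC 0.9 both are multiplied by √(1 + 4 × 0.9) = √4.6, giving 54.3% and 57.6%. The variance ratio is (1/8 + 1/4)/(1/6 + 1/6) = 1.125, an increase of 12.5%.

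**5. Facilitators.** At one per intervention network, 8 networks need 8 facilitators, two more than the six planned.

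**The case against.** The strongest reply is that the intended design is plain. The arm sizes in the recruitment sentence itself, the intervention arm section, the sample size section and the Results all give six intervention networks or 30 men per arm, and the Figure 4 caption also says one-to-one. Nothing in the article matches 8:4. On this view 2:1 and the 10 control indexes are wording errors, and the sequence may be correct. That may well be so. It does not remove the contradiction, which sits in the sentence that governs allocation, but it does limit what may be concluded.

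A reader might infer more than the article supports:

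- **That the trial is being randomized 2:1.** The article says only that REDCap generates and assigns the sequence. Neither the loaded ratio nor the randomization method is shown.
- **That the sample size or its precision fails.** The total of 60 and the stated margins do not change with the ratio, and the arm-difference margin changes only modestly.
- **That each arm has 36 men.** The phrase about five network members per index would allow this if the index were extra. The n=30 beside it, the inclusion of the index in the five under Intervention Arm, and the four others in the sample size section settle it at 30. The phrase is loose, not a separate conflict.
- **That facilitators would run short.** Their recruitment is reported as complete, but the number recruited is not given.

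**Conclusion.** The point holds as an internal contradiction in current text. The 2:1 ratio cannot be reconciled with 12 indexes in two arms of six, and 10 control indexes cannot be reconciled with a total of 12 split equally. The weight of the article favours 1:1 with 6 and 6, but the document alone cannot settle which ratio is in use.

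If 2:1 was loaded, the expected arms are 40 and 20 men, eight networks would need facilitators, and the margin for the arm difference at a 50% rate would widen by about 1.5 percentage points at zero correlation and about 3 points at 0.9. These figures assume five men per network, a common within-network correlation and the normal approximation. If 1:1 was loaded, the harm is confined to the wording. The matter still needs correcting, because the allocation ratio of a randomized trial has to be stated once and correctly, and the check costs very little.

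**What to change.** Check the ratio loaded in the REDCap allocation table, and compare it with any allocations already made.

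- **If it is 1:1:** in Recruitment, Screening, and Consent, replace 2:1 with 1:1 (6 and 6) and describe each network as the index plus 4 others. In the Figure 4 caption, change the number of control indexes from 10 to 6.
- **If it is 2:1:** restate the arms as 8 and 4 indexes (40 and 20 men) throughout, including the Abstract, the Figure 4 caption, Intervention Arm, Sample Size Justification and Results, and bring the number of facilitators into line. The pooled margins need no change on account of the ratio.

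The correction need not prescribe blocks that force 6:6. In an unblinded trial of 12 units, forced balance makes the last allocations predictable, and an article may leave that detail to the full protocol.

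The cost is one look at the allocation table and a few corrected phrases. An amendment is needed only if the loaded table differs from 6:6.
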